## Abstract

**Background:**

Data from a feasibility study suggest that the use of an inelastic, short-stretch compression bandage following total knee arthroplasty is a safe technique that may improve patient-reported health outcomes, and that it is feasible to recruit to a full-scale study.

**Methods:**

We will conduct a randomised controlled trial (RCT) of 2600 adult patients, which has 80% power to detect a 1 point difference in the Oxford Knee Score (a patient self-reported assessment of knee pain and function) at 52 weeks. Short stretch compression bandaging will be compared with standard wool and crepe bandaging following total knee arthroplasty. Recruitment will take place in orthopaedic units across the United Kingdom. Secondary outcomes include the EuroQol 5 Dimensions (EQ-5D)-5 L and EQ-5D-3 L scores, pain, length of hospital stay, and complications.

**Discussion:**

The Knee Replacement Bandaging Study (KReBS) is a large study which aims to contribute to the evidence base for informing clinical decisions for the use of compression bandaging following knee arthroplasty.

**Trial registration:**

International Standard Randomised Controlled Trial Register, ISRCTN 87127065. Registered on 20 February 2017.

**Electronic supplementary material:**

The online version of this article (10.1186/s13063-019-3344-1) contains supplementary material, which is available to authorized users.

## Background

Total knee arthroplasty (TKA) is a common and highly successful operation in the management of osteoarthritis [1]. Between 2003 and 2016 more than 870,000 entries for primary TKA were submitted to the 14th National Joint Registry report for England, Wales, Northern Ireland, and the Isle of Man [2]. Post-operative knee swelling is common and results in decreased functional performance which in turn can lead to delayed rehabilitation, an increase in length of hospital stay, and a decrease in patient satisfaction [3].

Compression bandage therapy is an established treatment of venous ulcers and lymphoedema, but efficacy in TKA remains unclear due to conflicting results in the literature and heterogeneous methodology. A feasibility study has been performed [4, 5] and data from that study suggested that the use of an inelastic, short-stretch compression bandage following TKA is a safe technique and that it was feasible to enlist surgical teams to recruit suitable patients. A large randomised controlled trial (RCT) is needed to establish effectiveness.

## Methods/design

This is a pragmatic, multicentre RCT investigating the use of a two-layer compression bandage system compared with a standard care (wool and crepe) bandage following TKA.

The study includes an economic evaluation.

### Objective

The objective is to determine the effectiveness and cost-effectiveness of a two-layer compression bandage compared with a standard wool and crepe bandage applied post-operatively on patient-reported outcomes in TKA patients.

### Setting

The Chief Investigator (CI) obtained initial agreements to participate from orthopaedic units in National Health Service (NHS) Hospital Trusts in the United Kingdom across a range of urban and rural areas with the provision of adding further interested centres. The pragmatic design of the trial and wide clinician involvement ensures immediate applicability and generalisability of the trial findings. Two thousand and six hundred patients will be recruited from approximately 26 secondary care orthopaedic units from across the UK. Table 1 shows a list of all participating hospital trusts sites that have been set up to recruit patients into the trial.

**Table 1 Tab1:** KReBS participating hospital trust sites

	Study sites
1.	Northumbria Healthcare NHS Trust
2.	Gateshead Health NHS Foundation Trust
3.	York Teaching Hospital NHS Foundation Trust
4.	North Cumbria University Hospitals NHS Foundation Trust
5.	The Dudley Group NHS Foundation Trust
6.	County Durham and Darlington NHS Foundation Trust
7.	Royal Devon and Exeter NHS Foundation Trust
8.	Hampshire Hospitals NHS Foundation Trust
9.	North Tees and Hartlepool NHS Foundation Trust
10.	East and North Hertfordshire NHS Trust
11.	East Kent Hospitals University NHS Foundation Trust
12.	South Tees Hospitals NHS Foundation Trust
13.	Maidstone and Tunbridge Wells NHS Trust
14.	Norfolk and Norwich University Hospitals NHS Foundation Trust
15.	Taunton and Somerset NHS Foundation Trust
16.	Manchester University NHS Foundation Trust
17	Warrington and Halton Hospitals NHS Foundation Trust
18.	Wrightington, Wigan and Leigh NHS Foundation Trust
19.	Western Sussex Hospitals NHS Foundation Trust
20.	City Hospitals Sunderland NHS Foundation Trust
21.	Dorset County Hospital NHS Foundation Trust
22.	Betsi Cadwalder University Health Board
23.	Golden Jubilee National Hospital
24.	Stockport NHS Foundation Trust
25.	University Hospitals Coventry and Warwickshire NHS Trust
26.	Epsom and St. Helier University Hospitals NHS Trust

### Study participants

Patients are eligible to participate in this study if they: 1) are scheduled for primary total knee arthroplasty; 2) present at a participating trial site; 3) are aged 18 years and over; and 4) are willing and able to provide written informed consent.

Patients will be excluded from this study if they: 1) are unable to provide informed consent; 2) have a history of peripheral vascular disease; 3) have a history of peripheral neuropathy; 4) have a history of, or current, venous ulceration; 5) have absent foot pulses; 6) are planned same-day discharge joint replacement patients; 7) are scheduled for revision knee arthroplasty; 8) are scheduled for Unicondylar or patellofemoral joint knee arthroplasty; 9) are prescribed regular concomitant high-dose anti-coagulant medication (patients on routine thromboprophylaxis can be included); 10) are unwilling to provide informed consent; 11) lack mental capacity and are therefore unlikely to comply with data collection; 12) are scheduled for bilateral knee replacement; or 13) have been previously recruited into KReBS (now scheduled for knee replacement on the opposite leg).

Additional clarification to accompany exclusion 9 was issued to participating sites as follows:This exclusion applies to high-risk patients, most likely with metal heart valves who require anticoagulation through the peri-operative period. These patients will usually be given intravenous heparin instead of their regular medications and should be clarified with the operating surgeon if unsure. In usual practice these will be rare.The vast majority of patients on anti-coagulation will be those taking warfarin, apixaban, rivaroxaban, etc. for deep vein thrombosis (DVT), atrial fibrillation (AF), or stroke prevention. They will have stopped this prior to the operation and will restart it following the operation. These patients should be included in the study.

### Trial interventions

#### Standard care (control) group

The bandage will be applied over the routine surgical wound dressing.

The control treatment is one layer of soft synthetic bandage applied from the proximal tibia to distal femur covered by a further layer of crepe bandage prior to or after tourniquet deflation, with 50% overlap of each layer. Cryotherapy can be applied over this if part of routine care. The bandage should be removed between 24 and 48 h post-operatively with the dressing remaining in situ.

#### Intervention group

The bandage will be applied over the routine surgical wound dressing. Intervention bandage is applied from the toes upwards. The application of the bandage from thigh to groin requires removal of the tourniquet first, keeping the leg elevated until the bandaging is complete.

Initially a foam inner bandage (Coban 2, 3 M UK) is applied from the toe to the groin on the affected leg with minimal overlap. The second layer of compression bandage (Coban 2, 3 M UK) is applied at 50% stretch and with a 50% overlap of bandage to ensure adequate compression in the application.

To ensure homogeneity in bandage application, the operating surgeons will be shown a training video on correct application. The compression bandage is removed on the planned day of discharge, at least 24 h following application. For patients not already discharged, the compression bandage will be removed at 48 (± 4) hours post-operation.

The bandages can be removed before 24 h if the patient finds them very uncomfortable, or in the event of clinical need or any adverse occurrence that would require their removal.

#### Rehabilitation

For both the intervention and standard care groups, patients will receive physiotherapy as per routine care.

### Outcome measures

Table 2 outlines the time points at which the outcomes are assessed. These outcomes are described below.

**Table 2 Tab2:** Study assessment schedule

	Study period						
	Enrolment	Allocation	Post-allocation				
Timepoint	Baseline (pre-randomisation)	Randomisation	Day of surgery	Approximately 10 days post-surgery	Week 4	Month 6	Month 12
Enrolment							
Eligibility screen	x						
Informed consent	x						
Allocation		x					
Interventions							
Compression Bandage			x				
Standard care Bandage			x				
Assessments							
Body mass index	x^a^						
Demographic data	x^a^						
Comorbidities	x^a^						
Oxford Knee Score	x^a^					x^a^	x
EQ-5D-3 L	x^a^					x^a^	x
EQ-5D-5 L	x						x
Pain scores (via SMS)				x	x		x
Basic health economics data (i.e. healthcare resource use)							x

*EQ-5D* EuroQol 5 Dimensions

^a^From routine data where possible

### Primary outcome

The primary outcome and end-point for the trial is the Oxford Knee Score (OKS) total score at 12 months from randomisation. OKS is a patient-reported outcome measure specifically designed and developed to assess function and pain after TKA surgery.

### Secondary outcomes

OKS at 6 months post-surgery.EuroQol 5 Dimensions (EQ-5D)-3 L index score at 6 months post-surgery.EQ-5D-3 L index score at 12 months post-randomisation.EQ-5D-5 L index score at 12 months post-randomisation.Pain scores at 10 days, 4 weeks, and 12 months post-surgery (collected via SMS message for those participants that opt into receiving SMS messages as part of the study).Length of hospital stay.Proportion of each patient group that: has to return to theatre within 30 days of surgery for any reason; is readmitted to hospital within 30 days of surgery for any reason; suffers a pulmonary embolism (PE) requiring inpatient hospitalisation within 30 days of surgery; suffers a DVT requiring inpatient hospitalisation within 30 days of surgery.

### Participant timeline

Figure 1 illustrates the process of enrolling participants into the study, the interventions being compared, and timing of assessments for the participants in the trial.

**Fig. 1 Fig1:**
[figure not shown]
KReBS study flow chart. Figure illustrating the process of enrolling participants into the study, the interventions being compared, and timing of assessments for the participants in the trial. BMI body mass index, EQ-5D EuroQol 5 Dimensions, OKS Oxford Knee Score, PROM Patient-Reported Outcome Measure

### Sub-studies

#### Text message

An embedded RCT will be undertaken to evaluate the effectiveness of a personalised text message prompt, including the participant’s name, compared with a standard text message on postal response rates to the 12-month questionnaire. This is separate to the collection of pain scores via SMS (all patients that consent to receiving text messages will be asked to return pain scores).

Text messages have been found to be effective for improving completion and return of questionnaires in trials [6]. Little research exists on the use of personalised text messaging for improving trial response rates.

Participants will be randomised in a 1:1 ratio to receive a standard text message, or to personalised text messages which includes their name with their 12-month follow-up questionnaire. Generation of the allocation sequence will be undertaken independently by a researcher not involved with the delivery of the text messages, and will use simple randomisation. Participants are able to opt out of receiving text messages without affecting participation in the main trial. Therefore, the sample size of the text sub-study will be constrained by the number of participants that consent to receiving text messages.

Participants will be sent the text messages at the same time as they are expected to receive their postal follow-up questionnaire (i.e. 2 to 4 days after the questionnaire is sent). Text messages are likely to be sent using secure UK-based text message gateway software such as that provided by Intelli Software (https://www.intellisoftware.co.uk/).

The primary outcome of this embedded trial will be the proportion of participants who return their questionnaire. Secondary outcomes will be time to response and completeness of response.

#### Pen sub-study

We will undertake an embedded RCT to evaluate the effectiveness of including a pen with the 12-month questionnaire on response rates. Participants allocated to the intervention group will receive a pen with the University of York logo on it, whilst control participants will receive no pen. Participants will be randomised using simple randomisation in a 1:1 ratio.

All participants in the KReBS main trial will be eligible to be included in the pen sub-study. There are no exclusion criteria.

The primary outcome will be the proportion of participants who return the 12-month questionnaire. Secondary outcomes will be time to response and completeness of response.

#### EQ-5D-3 L and -5 L order

We will undertake an embedded RCT to evaluate whether the order in which the EQ-5D-3 L and -5 L appear in the 12-month questionnaire impacts on the participant responses. Participants will be allocated using simple randomisation in a 1:1 ratio to either receive a questionnaire in which the EQ-5D-3 L appears before the -5 L, or a version in which the EQ-5D-5 L appears first. All participants due to be sent their 12-month questionnaire will be included in this embedded trial.

#### Northumbria blood loss sub-study

Blood loss during and following TKA reduces a patient’s haemoglobin and haematocrit counts whilst increasing the need for blood transfusion. It has been hypothesised that the use of a compression bandage will act as a tamponade and help reduce this loss [7]. Acute post-operative pain is also a concern and, from previous studies, compression bandaging may help decrease a patient’s post-operative pain [8].

A subset of main trial participants undergoing TKA in Northumbria NHS Foundation Trust will have their routinely taken pre- and post-operative full blood counts and transfusion data reviewed as well as the first 24 h post-operative pain scores and breakthrough analgesia requirements.

The primary outcome measure of the embedded blood loss sub-study will be the difference in haemoglobin level changes between the two arms. Secondary outcome measures will be the difference in haematocrit level changes and inpatient transfusion rates. Secondary endpoints, additional to those specified in the main trial protocol, will be length of stay, 24-h pain scores, and breakthrough analgesia requirement as well as readmission and complications rates.

Our initial sample size calculations were for 207 patients to observe a difference of 1 g of haemoglobin (90% power, SD 2.1). However, we adjusted this calculation to take into account the pre- and post-test correlation and a potential clustering around the surgeon.

A sample size of 156 (78 in each group) will give us 90% power to detect a difference in post-operative haemoglobin level (the primary outcome measure) between the intervention and control groups of 0.35 g/dl (SD 0.7, which equates to an effect size of 0.5), assuming a pre-post correlation of 0.7, 10% loss to follow-up, an average of 60 procedures per consultant, and an ICC of 0.01.

This sub-study is being undertaken as part of a student project and the results are to be reported separately to those of the main trial.

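### The blood-loss sub-study's adjusted sample size changes the haemoglobin SD from 2.1 to 0.7 and the target from 1 g to 0.35 g/dl, and the two stated adjustments explain neither change

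*Protocol article*

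**What the plan says.** All the figures stand in one section of the protocol article, Northumbria blood loss sub-study.

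- The starting point: "Our initial sample size calculations were for 207 patients to observe a difference of 1 g of haemoglobin (90% power, SD 2.1").
- The reason for revising it: "we adjusted this calculation to take into account the pre- and post-test correlation and a potential clustering around the surgeon".
- The result: "A sample size of 156 (78 in each group) will give us 90% power".
- The revised target and SD behind that result: "0.35 g/dl (SD 0.7, which equates to an effect size of 0.5").
- The further inputs are r = 0.7 between the pre- and post-operative values, a 10% allowance for dropout, 60 operations for each consultant and an intracluster correlation of 0.01.
- The primary outcome of the sub-study "will be the difference in haemoglobin level changes between the two arms", whereas the power statement refers to the post-operative haemoglobin level.

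The Randomisation section says that patients are allocated individually, 1:1, without stratification or blocking. The main trial's Sample size section mentions no allowance for clustering.

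**The concern.** The second calculation is presented as the first one with two refinements. A pre-post correlation enters as a multiplier on the sample size, and so does a design effect. Neither alters the raw SD of haemoglobin or the difference the study wants to detect. Yet the SD falls to a third of its initial value and the target to about a third, with no explanation of either change. The reader is left with two SDs for what appears to be the same measurement.

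This matters because the power claim for 0.35 g/dl depends almost entirely on which SD is right. The sub-study is to be reported separately from the main trial, so its power statement has to stand on its own.

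A secondary question is the clustering term. It follows the formula for cluster-randomised trials, although patients here are randomised individually.

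**Working it through.** **Inputs.** From the sub-study section: 207 patients, 1 g, SD 2.1, 90% power; 156 patients (78 per arm), 0.35 g/dl, SD 0.7, r = 0.7, 10% loss, 60 procedures per consultant, ICC 0.01. Assumed: 1 g means 1 g/dl; the two-sided 5% level given for the main trial under Statistical analysis also applies here; the 10% loss also lies behind the 207.

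**1. Initial figure.** n per arm = 2 × (1.96 + 1.2816)² × 2.1² / 1² = 92.7, so 93; total 186; 186 / 0.9 = 206.7, so **207**. It reproduces.

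**2. Adjusted figure.** Effect size 0.35 / 0.7 = 0.5 needs 86 per arm (t-based). Correlation factor: 1 − 0.7² = 0.51. Design effect: 1 + (60 − 1) × 0.01 = 1.59. Then 86 × 0.51 × 1.59 / 0.9 = 77.5, so **78 per arm, 156 in total**. It reproduces. The normal approximation without intermediate rounding gives 84.06 × 0.51 × 1.59 / 0.9 = 75.7, so 76 per arm, within 3%.

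The 0.51 factor is needed to reach 78, so 0.7 was used as a raw SD.

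**3. Can the correlation turn 2.1 into 0.7?** At r = 0.7:

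- residual SD = 2.1 × √0.51 = 1.50
- change-score SD = 2.1 × √(2 × (1 − 0.7)) = 2.1 × √0.6 = 1.63

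Reaching 0.7 would need r = √(1 − (0.7/2.1)²) = 0.943 for a residual SD, or r = 1 − (0.7/2.1)²/2 = 0.944 for a change SD. The plan states 0.7.

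**4. What the stated adjustments alone would give.** Keeping SD 2.1 and 1 g: 92.68 × 0.51 × 1.59 / 0.9 = 83.5, so 84 per arm, **168** in total. With SD 2.1 and 0.35 g/dl: 756.5 × 0.51 × 1.59 / 0.9 = 681.6, so 682 per arm, **1364** in total.

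**5. Power of 156.** Effective n per arm = 78 × 0.9 / 1.59 = 44.15 with the design effect, and 78 × 0.9 = 70.2 without it. Standard error = SD × √0.51 × √(2/n). Power is from the noncentral t distribution; the normal approximation gives values up to about one percentage point higher.

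| Raw SD | Target (g/dl) | Power with design effect | Power without |
|---|---|---|---|
| 0.7 | 0.35 | 90% | 98.5% |
| 1.0 | 0.35 | 62% | 82% |
| 1.5 | 0.35 | 33% | 48% |
| 2.1 | 0.35 | 19% | 28% |
| 2.1 | 1 | 87% | 97.5% |

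If 0.7 is already the SD of the analysed quantity (residual or change), the 0.51 factor must not be applied. The standard error is then 0.7 × √(2/44.15) = 0.149, the ratio is 0.35 / 0.149 = 2.35, and power is about **64%** with the design effect.

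**6. Difference detectable with 156 at 90% power.**

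| Raw SD | With design effect | Without |
|---|---|---|
| 2.1 | 1.05 g/dl | 0.83 g/dl |
| 0.7 | 0.35 g/dl | 0.28 g/dl |

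**The case against.** The best defence is that nothing is miscalculated. The 156 and the 90% follow from the SD of 0.7 given in the same sentence, and the 207 follows from its own inputs. This stands: the fault is an unexplained change of inputs, and a reader who inferred an arithmetic error or a power claim at odds with the SD it uses would be wrong.

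It can also be said that the 19% is a worst case. It joins the initial SD to the revised target, a pairing the plan never makes. The SD and the target fall almost in proportion, so the standardised effect hardly moves (1 / 2.1 = 0.476 against 0.5), and 156 is close to the 168 needed for the initial pair. This stands too. A reader might infer that the sub-study is badly underpowered whatever it targets. The documents do not support that, since at SD 2.1 it still has about 87% power for 1 g.

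On clustering, the plan speaks only of a potential effect. Operating surgeons are shown a training video to make bandage application uniform (Intervention group section), so the treatment effect might vary by surgeon, and that variation would not cancel. It would go too far to say that there is no clustering to allow for. What remains is narrower: under individual randomisation with surgeons treating both arms, a surgeon effect common to both arms does not need the 1.59, and including it raises the number, which is conservative.

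Finally, this is a student project reported apart from the main trial, and a journal article may leave the source of an SD to the full protocol. The absence of a source is therefore not the finding. The two conflicting SDs are printed here.

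**Conclusion.** The concern holds as an unreconciled change of inputs. The section describes one calculation as an adjustment of another, but the SD falls threefold and the target from 1 g to 0.35 g/dl, and correlation and clustering explain neither.

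The 90% power for 0.35 g/dl rests on 0.7 being a raw SD. It drops to about 64% if 0.7 is a residual or change SD, and to about 19% if the raw SD is 2.1. The section's two descriptions of the outcome, as a change and as a post-operative level, leave the type of SD unclear. What is uncertain is the absolute difference that 156 patients can detect. The documents do not show which SD is correct.

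The clustering factor is secondary and works in the other direction: without it, power at SD 0.7 would be about 98%.

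These results rest on the assumptions listed with the inputs and on a baseline-adjusted analysis with r = 0.7. The main trial's sample size and primary analysis are not affected.

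**What to change.** 1. Reconcile 2.1 with 0.7. State one raw SD of haemoglobin in g/dl, say explicitly that it is raw, and use it throughout. If the SD and the target were deliberately revised, say so and give the reason, separately from the two adjustments.
2. Give the initial target in the same unit as the revised one, and describe the outcome in one way, as a change or as a baseline-adjusted post-operative level.
3. Restate the difference that 156 patients detect at 90% power under the chosen SD, using the figures in the last table of the working.
4. Label the factor 1.59 as a conservative allowance, or leave it out of the stated power.

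The cost is one rewritten paragraph. The detectable difference may look less favourable if 2.1 proves to be the right SD. Enrolment does not change.

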### Randomisation

Simple, equal randomisation without stratification or blocking will be used to generate the treatment allocation schedule. As the sample size of the trial exceeds 200 there is no loss of statistical efficiency compared with using more complex (restricted) randomisation methods [9].

When patients have given consent and their baseline forms have been completed, the Research Nurse or recruiting clinician will randomise them using the York Trials Unit’s (YTU) secure, web-based randomisation service. Patients will be allocated 1:1 to receive either compression bandaging or standard care (wool and crepe) bandaging, therefore ensuring allocation concealment and immediate unbiased allocation. Patients will be informed of their allocations as will the clinician managing each patient.

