### Statistical analysis

A detailed analysis plan will be agreed with the combined Trial Steering Committee (TSC) and Data Monitoring and Ethics Committee (DMEC) at an early stage of the study, before all of the data have been collected. Any subsequent amendments will be clearly stated and justified. Analyses will be conducted following the principles of intention-to-treat (ITT) with outcomes analysed according to the patients’ original, randomised group irrespective of deviations based on non-compliance, and significance tests will be two-sided at the 5% level, unless otherwise stated.

The primary analysis will compare total OKS scores between the treatment groups at 12 months using a covariance pattern mixed model incorporating outcome data at 6 and 12 months, adjusting as fixed effects for age, gender, baseline score, time point, treatment group, and a treatment group-by-time point interaction, and hospital site as a random effect. Treatment effects in the form of an adjusted mean difference will be presented with an associated 95% confidence interval (CI) and *p* value for both time points (6 and 12 months). The primary end-point will be the treatment effect estimate at 12 months, while the treatment effect at 6 months will serve as a secondary outcome. Pain score (at 10 days, 4 weeks, and 12 months) will be analysed similarly.

The proportion of participants who, within 30 days of surgery, 1) return to theatre, 2) are readmitted to hospital, 3) experience a PE requiring hospitalisation, and 4) experience a DVT requiring hospitalisation will be compared between the two groups using mixed effects logistic regression models, adjusting for age and gender as fixed effects, and hospital site as a random effect. The treatment effect in the form of an odds ratio will be presented with an associated 95% CI and *p* value.

Length of hospital stay in days will be analysed via a mixed effect Poisson, or negative binomial, regression model as appropriate, adjusting for age and gender as fixed effects, and hospital site as a random effect. An incidence rate ratio, 95% CI and *p* value will be provided.

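### The blood-loss sub-study sizes itself with a whole-cluster design effect of 1.59 although patients are individually randomised, so its stated 90% power for 0.35 g/dl does not fit its design (the error is conservative)

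*Protocol article*

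**What the plan says.** The protocol article's section on the Northumbria blood loss sub-study first mentions 207 patients and then says that "we adjusted this calculation to take into account the pre- and post-test correlation and a potential clustering around the surgeon". The revised figure is: "A sample size of 156 (78 in each group) will give us 90% power to detect a difference in post-operative haemoglobin level". The target difference is "0.35 g/dl (SD 0.7, which equates to an effect size of 0.5", and the remaining inputs are listed as "assuming a pre-post correlation of 0.7, 10% loss to follow-up, an average of 60 procedures per consultant, and an ICC of 0.01".

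The sub-study population is "A subset of main trial participants undergoing TKA in Northumbria NHS Foundation Trust". The Randomisation section says how they are allocated: "Simple, equal randomisation without stratification or blocking will be used to generate the treatment allocation schedule", and "Patients will be allocated 1:1 to receive either compression bandaging or standard care (wool and crepe) bandaging". No passage allocates surgeons to arms or restricts a surgeon to one type of bandage.

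**The concern.** The inflation 1 + (m − 1) × ICC is the variance penalty when all patients of a cluster receive the same treatment. Differences between clusters then become differences between arms. With patient-level randomisation, each surgeon can be expected to contribute patients to both arms. A surgeon whose patients lose more blood on average then raises blood loss in both arms, and that shared effect largely drops out of the contrast.

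What is at stake is the stated link between 156 patients, 0.35 g/dl and 90% power. The sub-study is to be reported separately from the main trial, so its readers will take this paragraph as its design statement. They would be told that it was built to detect 0.35 g/dl when, on the same inputs, it can detect a smaller difference with the same power.

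**Working it through.** **Inputs.** From the sub-study section: difference 0.35 g/dl, SD 0.7 (standardised difference 0.5), power 90%, pre-post correlation 0.7, 10% loss, 60 procedures per consultant, ICC 0.01. From the Statistical analysis section, written for the main trial and assumed to apply here: "significance tests will be two-sided at the 5% level, unless otherwise stated".

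**Step 1: reproduce 156.**
- Two-sample t-test, standardised difference 0.5, 90% power: 85.03 per arm, rounded up to 86.
- Baseline adjustment (ANCOVA): 1 − 0.7² = 0.51.
- Design effect: 1 + (60 − 1) × 0.01 = 1.59.
- Loss: divide by 0.9.
- 86 × 0.51 × 1.59 / 0.9 = 77.5, so 78 per arm and 156 in total, exactly as stated.

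The normal approximation with the same factors gives 152 to 154. Leaving out the 1.59 gives 98 (86 × 0.51 / 0.9 = 48.7, so 49 per arm). A change-score analysis gives 116 without the factor and 184 with it. So the 1.59, which the article does not print, was evidently applied.

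**Step 2: the factor for this design.** Take a surgeon effect with variance ICC × σ² that is common to both arms. If each surgeon's patients split about equally between arms, this effect cancels from the difference in means. The remaining variance is (1 − ICC) × σ², a factor of 0.99 with surgeon adjustment and about 1.0 without it. A simulation with 140 analysed patients, simple randomisation, ICC 0.01 and 3 surgeons (assumed from 156 / 60 = 2.6) gave 98.3% power both with and without surgeon adjustment.

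**Step 3: power with 156 recruited.** Evaluable patients per arm: 78 × 0.9 = 70.2. The effective SD is 0.7 × √(analysis factor × design factor). The analysis factor is 0.51 for baseline adjustment and 2 × (1 − 0.7) = 0.60 for a change score. The design factor 1.29 = 1 + (30 − 1) × 0.01 treats each surgeon-by-arm group of about 30 patients as its own cluster. The article does not state that reading; it is shown as an allowance for treatment effects that differ between surgeons. Power is by the t-test.

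| Analysis | Design factor | Total needed for 90% | Power at 156 for 0.35 g/dl | Detectable at 90% power |
|---|---|---|---|---|
| Baseline-adjusted | 1.59 | 156 | 90.4% | 0.35 g/dl |
| Baseline-adjusted | 1.29 | 126 | 95.2% | 0.31 g/dl |
| Baseline-adjusted | 1.00 | 98 | 98.5% | 0.28 g/dl |
| Change score | 1.29 | 148 | 91.7% | 0.34 g/dl |
| Change score | 1.00 | 116 | 96.7% | 0.30 g/dl |

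Hand check of the 0.28: effective SD 0.7 × √0.51 = 0.50; 0.50 × √(2/70.2) × (1.96 + 1.28) = 0.27 by the normal approximation, and 0.275 by the t-test.

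**The case against.** **The sum is right.** The figure of 156 follows from the stated inputs, so a reader might infer a slip in calculation where there is none. This stands. The fault is the choice of design effect.

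**The allowance is disclosed and conservative.** The cluster size and ICC are printed, and power on the design's own terms is above 90%. This also stands. A reader might infer that the sub-study is underpowered, but every row with a factor of 1.00 or 1.29 is above the target.

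**Surgeons may still matter.** Randomisation within surgeon does not remove variation in the treatment effect between surgeons. The Intervention group section has surgeons shown a training video so that bandaging is uniform, which suggests that surgeon-dependent delivery was foreseen. Some allowance is therefore defensible, and with a change score and a factor of 1.29 power falls to 91.7%, close to the stated 90%. But the article gives no such rationale, and the whole-cluster factor is not the way to express it.

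**No single replacement figure is safe.** One might infer that the true power is simply 98%. The section describes the primary outcome once as a change in haemoglobin and once as the post-operative level, so the answer depends on the analysis. It also depends on the correlation: at an assumed 0.5 instead of 0.7, baseline-adjusted power without inflation is 92.4%.

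**Two further inferences are not supported.** The 98 in the working might suggest that the sample can be cut. That would remove a useful margin for no benefit, since the data are routine and the patients are already in the main trial. One might also suppose that √1.59 = 1.26 would carry into the analysis and widen the confidence interval by 26%. No passage proposes this, and the main trial handles hospital site by a random effect.

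**Conclusion.** The point holds as a minor one. The stated 90% power at 0.35 g/dl rests on a design effect for whole-cluster allocation that this individually randomised sub-study does not have. With no inflation and the plan's other inputs, 156 patients give about 98% power (detectable difference about 0.28 g/dl) with baseline adjustment, or about 97% (about 0.30 g/dl) with a change score. The gap from the stated power is about 7 to 8 percentage points, in the safe direction.

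This rests on three assumptions: a two-sided 5% level carried over from the main trial; surgeons treating patients in both arms, which is inferred from the randomisation scheme and not stated outright; and no material variation in the treatment effect between surgeons. The main trial's sample size and primary analysis are not affected.

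**What to change.** Keep 156 and remove the 1.59 factor from the sub-study's sample-size paragraph. Then:

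- State which analysis the power refers to. For post-operative haemoglobin adjusted for baseline, give about 98% power for 0.35 g/dl, or 90% for about 0.28 g/dl. For a change score, give about 97%, or 90% for about 0.30 g/dl.
- If an allowance for treatment effects that vary between surgeons is wanted, name it as that and give its assumption. For example, an assumed surgeon-by-arm factor of 1.29 gives about 95% with baseline adjustment.
- Account for surgeon in the analysis as a covariate or random effect.

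The cost is rewording one paragraph and one term in the sub-study's model. No extra patients or data are needed.
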